### Allocation to trial arms and treatment

#### Randomisation

Pharmacists will randomise smokers by sealed envelopes. Block randomisation stratified by pharmacy will be used with two blocks of 4 to ensure randomisation to each arm in every pharmacy that recruits at least 4 participants. Although blocks of 4 could become predictable, no pharmacist will recruit sufficient participants to discern the pattern. Telephonists conducting follow up will be blind to treatment allocation but this is an open label trial and participants and therapists will know which arm they are in.

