## Methods/Design

### Participant Recruitment

Pharmacists who work for NHS stop smoking services will be recruited from areas of high smoking prevalence in Birmingham and Yorkshire region; those treating at least four new smokers for cessation per month will be eligible. Over 60 pharmacists in Birmingham see this many patients in the NHS stop smoking service and most are recruited by brief interventions across the counter, thus providing a naturalistic setting in which to test the implementation of reduction programmes and integration with other smoking cessation efforts.

We plan to recruit 10 pharmacies and for each to recruit four participants into a reduction programme each month, providing a quota of 16 in four months. We plan two waves of recruitment. Using two waves will allow us to learn lessons from the first wave, which is consistent with the developmental nature of this trial.

Educational outreach visits are effective in changing GP's behaviour [10]. We will make visits to local GPs to inform them about the programme and encourage them to refer reluctant quitters to the reduction programme. GPs will be given referral cards for their local pharmacy provider to give to patients. If the recruitment of participants is particularly slow during the either wave, GP's will be asked to send a letter to their registered current smokers. The letter will inform them that the reduction programme is available at their local pharmacy. It will also give details of how they can take part, should they want to, along with an information leaflet about the study.

Pharmacists will be asked to recruit participants opportunistically as well as receiving referrals from GPs. To assist opportunistic recruitment, pharmacists will display a poster in the window. Pharmacists will be compensated for their time with service support funding.

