### Sample size

This is a pilot trial designed to test the processes, examine implementation issues, and reactions to the programme of those involved. We estimated a sample size of 160 participants recruited in 10 pharmacies would be sufficient to test the feasibility of the study. The outcomes therefore include the percentage of pharmacists that agree to participate, the percentage that are trained, the percentage that actually recruit smokers into reduction programmes. Our most important efficacy outcome (because it is linked with unequivocal health benefits) is smoking cessation. We will record the weekly recruitment rate of patients into the reduction programmes and into NHS stop smoking programmes, comparing the rate of recruitment into stop smoking programmes for pharmacists participating in the trial with those not doing so. This will give evidence on whether smokers are being diverted by reduction. For smokers in each type of programme, we will record the number of contacts made, the time of the pharmacist used in delivering the programmes, the amount of NRT used in each arm, the number of people that try to quit, and the number of people that attend the pharmacist for post-cessation support as a proportion of those that try to quit. We will measure the fidelity to each programme by recording some consultations and analysing their content against the schedule of proposed content. We will record sustained smoking reduction and abstinence, although the trial is not powered to detect worthwhile differences in the abstinence outcomes. Four week and six month abstinence rates will be measured following the Russell standard. We will record the proportion of people that complete the webform/telephone follow up.

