Any trial to test the role of behavioural support and shorter versus standard length reduction programmes would need to use six month prolonged smoking abstinence as the outcome [11,12]. A sample of 160 participants is not large enough to provide definitive evidence of efficacy with such an outcome because our systematic review showed that standard length programmes lead to about 7% of participants sustaining six month abstinence [13]. However, we assume that shorter reduction programmes are about twice as effective, as suggested by the Haustein trial. Our most important efficacy outcome here is four week abstinence. Based on our systematic review, we expect about 7% of participants who follow the standard length programme with behavioural support to sustain abstinence for six months, which equates to about 21% achieving 4 weeks of abstinence, our main efficacy outcome. Based on this, we get the following table, which shows that this sample size will have 80% power to detect a rate ratio of 1.7 or 90% power to detect a rate ratio of 1.8 (Table 1), lower than observed in Haustein.

**Table 1 T1:** Efficacy of shorter reduction programmes versus standard length

			80% power	90% power
**Base quit proportion**	**RR**	**Quit proportion in intervention**	**N in each arm**	**N in each arm**

0.21	1.7	0.357	146	195

0.21	1.8	0.378	114	152

0.21	1.9	0.399	91	122

The following are also considerations in the sample size. If we take key process measures like attendance for behavioural support sessions as 63% (observed in the review), with 80 smokers receiving behavioural support, we could estimate this with +/-7% precision with 80% confidence. Asking each pharmacy to treat 16 patients, 4 in each arm, will give a reasonable range of experiences for them and us to evaluate the programmes.

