#### Behavioural intervention

This is a 2 × 2 randomised factorial design trial of behavioural support versus no support and short versus standard length reduction programme (Figure 1). It is a pilot study for a later definitive trial.

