### Length of study

We plan to recruit 10 pharmacies. If they each recruit four participants per month, they will recruit their quota of 16 in 4 months. We plan two waves of recruitment, with final follow up of that cohort one year after the end of recruitment. The second wave of pharmacies will begin recruiting approximately six months after the first wave of recruitment. In total the duration will be 30 months.

The end of the trial is defined as last contact with any trial participant.

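### The randomisation rule of two blocks of 4 does not match the quota of 16 per pharmacy, and its reassurance about predictability fails for any pharmacy that meets that quota

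*Protocol article*

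**What the plan says.** The Randomisation section has pharmacists allocate participants from sealed envelopes. Allocation is blocked and stratified by pharmacy, using "two blocks of 4 to ensure randomisation to each arm in every pharmacy that recruits at least 4 participants". The section concedes that blocks of this size might become predictable, then answers that "no pharmacist will recruit sufficient participants to discern the pattern". The same section says the trial is open label, so therapists know the allocations; only the follow-up telephonists are blind.

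Other sections set a larger number per pharmacy:

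- Participant Recruitment: four participants a month, "providing a quota of 16 in four months".
- Length of study: "If they each recruit four participants per month, they will recruit their quota of 16 in 4 months".
- Sample size: "Asking each pharmacy to treat 16 patients, 4 in each arm", and "We estimated a sample size of 160 participants recruited in 10 pharmacies would be sufficient".

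There are four arms: "This is a 2 × 2 randomised factorial design trial of behavioural support versus no support and short versus standard length reduction programme". The pharmacist also recruits across the counter (Participant Recruitment) and gives the behavioural support (Supported standard programme).

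**The concern.** There are two problems. First, the number of allocations implied by the block rule is half the number each pharmacy is meant to use. Whoever prepares the envelopes cannot tell from the article what follows the eighth.

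Second, the only defence offered for small fixed blocks is low recruitment, and the plan's own target contradicts it. With four arms, a block of 4 is one of each arm, and stratification by pharmacy means each pharmacy sees the whole sequence for its stratum. The person who decides whom to approach, and when, also knows the earlier allocations and will deliver the treatment. The arms differ greatly in workload: eight scheduled support contacts against a leaflet. Counter recruitment makes it easy to delay one customer or bring another forward.

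If keener smokers were steered in this way, the distortion would fall on the support contrast, the programme-length contrast, or both. Both are listed as primary objectives, and the Statistics section says updated estimates will set the sample size for the definitive trial. Intention-to-treat analysis and sensitivity analyses for missing data do not remove selection at entry.

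**Working it through.** **Inputs.** Block size 4 and two blocks (Randomisation); four arms (Behavioural intervention); 16 per pharmacy and 4 per arm (Sample size); 4 per month for 4 months (Length of study); 10 pharmacies and 160 participants (Sample size).

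**The quota agrees with itself.** 4 per month × 4 months = 16. 16 ÷ 4 arms = 4 per arm. 16 × 10 pharmacies = 160.

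**The block rule does not reach it.** 2 blocks × 4 = 8 per pharmacy, or 8 ÷ 4 = 2 per arm. Over 10 pharmacies, 8 × 10 = 80, against 160.

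**Readings that would close the gap.** Four blocks of 4 = 16; two blocks of 8 = 16; two blocks of 4 in each of two waves at the same pharmacy = 16; 20 pharmacies × 8 = 160. The article states none of these. Length of study describes the second wave as a wave of pharmacies, so it does not give one pharmacy a second pair of blocks.

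**Blocks completed.** 16 ÷ 4 = 4 complete blocks at quota; even 8 recruits complete two.

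**Predictability with fixed blocks of 4, one of each arm, block size known or inferred.**

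- Certain beforehand: the fourth place in each block, so 1/4 = 25% of arm allocations (the 4th, 8th, 12th and 16th).
- Best guess of the arm: (1/4 + 1/3 + 1/2 + 1) ÷ 4 = 0.521, or 8.3 of 16, against 0.25 by chance.
- Best guess of support versus no support: the chances by place are 1/2, 2/3, 2/3 and 1. At the third place, the first two allocations share the factor level with probability 1/3 (next one certain) and differ with probability 2/3 (even odds), giving 1/3 + 2/3 × 1/2 = 2/3. The mean is (1/2 + 2/3 + 2/3 + 1) ÷ 4 = 0.708, against 0.50.

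**What other block schemes achieve.** Here the guesser always names the arm (or factor level) used least so far, over 16 participants.

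| Scheme | Arm guessed | Support guessed |
|---|---|---|
| Fixed 4 | 52% | 71% |
| 4 and 8 in random order from the start | 48% | 67% |
| Fixed 8 | 47% | 67% |
| Unrestricted | 25% | 50% |

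A list of exactly 16 that must begin with a 4 and contains one 8 gains a little less: (8 × 0.521 + 8 × 0.470) ÷ 16 = 0.495 for arm and (8 × 0.708 + 8 × 0.666) ÷ 16 = 0.687 for support.

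**Cost of opening with a block of 8.** Such a block holds two of each arm. The chance that its first four places cover all four arms is 2⁴ ÷ C(8,4) = 16 ÷ 70 = 0.229. A pharmacy stopping at four recruits would then lack at least one arm 77% of the time.

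**The case against.** The strongest reply is that the sentence gives a purpose for the two blocks, namely to protect pharmacies that recruit few people, and does not say the list ends at 8. They may be opening blocks with more to follow, or the wording may be loose for two larger blocks. A journal article may leave the full schedule to the longer protocol. This stands. A reader might infer that the trial would run out of envelopes or fall 80 participants short; the text does not show that. It shows a mismatch to be reconciled.

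A reader might also infer that pharmacists will know every fourth allocation, or that selection bias is present. The article does not say that pharmacists are told the block size, nor whether envelopes are opaque or numbered. The percentages hold only for someone who knows or infers the block structure and tracks it.

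The reassurance refers to a pharmacist, whereas the quota is per pharmacy and is a target. The qualitative section expects some pharmacists to recruit few or none, and a pharmacy with fewer than four recruits completes no block. This softens the conflict but does not remove it: the safeguard works only where recruitment falls well short of plan.

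Finally, this is a feasibility pilot, which the Sample size section says is not powered for worthwhile differences in abstinence, and the authors weighed the block-size risk openly. That lowers the severity. It does not dispose of the point, because both factorial comparisons are primary objectives and testing trial processes is part of the pilot's purpose.

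**Conclusion.** The point holds in two parts. As written, the block rule gives 8 allocations per pharmacy (2 per arm) against a planned 16 (4 per arm), and the sections must be reconciled. Separately, the statement that the pattern cannot be discerned is not tenable for a pharmacy that meets its quota, since it completes four blocks that each contain every arm once.

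If the pharmacist knows or infers the block size, up to 25% of arm allocations are certain beforehand, and best-guess rates are 52% for arm and 71% for support. These figures assume fixed blocks of 4, one of each arm, and full sight of earlier allocations in that pharmacy. They bound predictability; they do not estimate a bias. Given the pilot setting, this should be fixed before envelopes are issued, but it does not invalidate the design.

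**What to change.** 1. State that each pharmacy's list holds 16 allocations, 4 per arm.
2. Begin every list with a block of 4, which keeps the stated guarantee of each arm by the fourth recruit. Then use blocks of 4 and 8 in random order (for example 4-8-4, 4-4-8 or 4-4-4-4), and withhold block sizes from pharmacists.
3. Delete the sentence saying that the pattern cannot be discerned.
4. Have the existing trials unit release each allocation only after consent and baseline data are logged. If envelopes are kept, number and log them, and open each only at that point.

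Do not use two fixed blocks of 8 or any list that opens with an 8. They match the quota, but only 23% of pharmacies stopping at four recruits would then have every arm.

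The cost is a regenerated list and a small logging step. Mixing block sizes alone gains little: the arm guess rate falls from 52% to about 48% with free mixing, and to about 50% when the list must open with a 4. Release after enrolment is therefore the main protection, because it stops anyone seeing the next allocation or reordering people once it is seen. It does not stop a guess made before a customer is approached, which is why block sizes should be withheld as well.

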#### Behavioural intervention

This is a 2 × 2 randomised factorial design trial of behavioural support versus no support and short versus standard length reduction programme (Figure 1). It is a pilot study for a later definitive trial.

**Figure 1 F1:**
[figure not shown]
**Randomised factorial design trial (2 × 2) of behavioural support versus no support on smoking reduction**.

All participants will receive NRT and be randomised to either behavioural support or no support and either standard length or short reduction; approximately 80 people in each arm.

### Behavioural support arms

#### Supported standard programme

The behavioural support schedule will follow that used in the Nicorette industry trials, providing support and monitoring at baseline, 2, 6, 10, 16, 22, 28, and 34 weeks. The pharmacist giving support in a consulting room will invite participants to set a treatment goal and provide advice on how to reduce cigarettes using unstructured or structured methods of smoking reduction. Unstructured smoking reduction means that participants were not guided as to which cigarettes to eliminate but are left to experiment themselves and without a specific goal except 50% reduction by 6 weeks. Structured reduction means having specific sequential goals for either reducing cigarettes per day or reducing smoking periods. The cigarettes per day methods are either smoke-free periods (SFP) or lengthen the inter-cigarette interval, i.e. the timer method [14,15]. Smoke-free periods concentrates on times when smoking is allowed and when it is not, but the number of cigarettes is not restricted. In the timer method the number of cigarettes per day is restricted and also times when smoking is allowed.

#### Supported short programme

Participants in the 4-week supported programme will be given the same advice and help with reduction but this will be provided on a different schedule. Participants will be seen weekly for four weeks with the aim of reducing smoking to achieve cessation by the end of four weeks. If this fails, reducing to induce cessation at 8 weeks will be the goal. Thereafter, consistent with the pragmatic nature of this trial, participants in the short reduction arm will be allowed to follow the standard reduction regime. Behavioural support will be provided at baseline, weekly to 4 weeks, 6, 8, and 16 weeks i.e. the same number of visits but on a different schedule.

### No support arms

Participants in the no support arms will not be given advice or support by the pharmacist. Instead they will be given a leaflet that describes the reduction programmes (unstructured, cigarettes per day, or smoking periods) and which gives brief advice on using one or more of these approaches, and encourages use of NRT to support this. Participants will be advised to reduce on a schedule that follows the standard programme, if randomised to that arm, or the short programme, if randomised to that arm. The leaflet will advise participants to return to the pharmacy for more NRT to support reduction as needed. This will be dispensed on NHS prescription (following the primary care trust's patient group direction). The outcomes will be monitored without personal visits to avoid the possibility that these are contributing to adherence to the programme.

### Transferring to the cessation programme

The aim of the reduction programme is to help people reduce and pharmacists will be encouraged not to pressure people to stop smoking, while explaining that proven health benefits derive from smoking cessation rather than reduction. However, most people who want to reduce smoking want to do so as a way of stopping [16,17], though rarely with a predetermined timetable. It is for the therapist and the patient to determine whether and when a person is transferred to the cessation programme. Pointers towards possible cessation are:

• Increased confidence that the patient can control her/his smoking.

• Cigarette consumption has fallen to five per day or fewer, or the person is going most of the day without smoking.

Participants in the No-support arms will be asked about their quitting attempt when they return to the pharmacy for more NRT. A key principle of the whole reduction approach is that failed quit attempts do not lead to an end of the programme. If a person moves to cessation and the quit attempts fails, they can resume the reduction programme and continue to control their smoking until they are ready to stop again.

### Length of study

We plan to recruit 10 pharmacies. If they each recruit four participants per month, they will recruit their quota of 16 in 4 months. We plan two waves of recruitment, with final follow up of that cohort one year after the end of recruitment. The second wave of pharmacies will begin recruiting approximately six months after the first wave of recruitment. In total the duration will be 30 months.

The end of the trial is defined as last contact with any trial participant.

### Trial Outcomes

This is a pilot trial designed to test the processes, examine implementation issues, and reactions to the programme of those involved i.e. whether pharmacists can be trained to implement the reduction programme, how well they do so, and how this is received by smokers and by pharmacists. These processes will be measured by:

• The percentage of pharmacists that agree to participate and the percentage that are trained and pass an assessment of competence.

• The monthly recruitment rate of patients into reduction programmes and into NHS stop smoking programmes, comparing the rate of recruitment into stop smoking programmes for pharmacists participating in the trial with those not doing so.

• Recording of some consultations and analysing their content against the schedule of proposed content.

• The proportion of people that would recommend the smoking reduction programme to another smoker and their views on the way that it ran, taken from the 12 month evaluation questionnaire.

We will also examine whether behavioural support is more effective than no support and will investigate whether shorter reduction programmes are more effective than standard length reduction programmes. This will be achieved by measuring self-reported sustained smoking reduction and abstinence. Smoking cessation outcomes will be measured from the time of quitting and we will measure 4 week and 6 month prolonged abstinence following the Russell standard, i.e. by intention to treat and biochemically confirmed [12]. Thus abstinence will be defined as allowing a two week grace period after quit day in which smoking lapses do not count against abstinence and from day 15 onwards, no more than five cigarettes have been smoked. This will be verified by a CO < 10 ppm. Smoking reduction will be assessed by the proportion of people that reduce their consumption to < 50% of baseline value, the mean cigarette consumption at the end of the trial.

As this is a preliminary trial, we will record data to allow us to assess whether the processes of the trial need improvement prior to a definitive trial. We will also examine data on adverse events and drop outs from the programme (Appendix 1).

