### Follow up procedures

We propose testing the feasibility of using a follow up method that is unlikely to be perceived by participants as providing them with behavioural support or enhance motivation to adhere. This will be by email/Webform emailed monthly for the 12 months of a participant's involvement in the trial. Monthly follow up will ensure that we can assess whether smokers have started their period of abstinence and schedule verification visits, based on a process outlined for trials of this kind [18]. Web follow up has achieved > 90% follow up in a previous trial [19]. Based on our experience of trials in smokers' clinics, most patients have email addresses and these are useful for follow up. Text reminders will be sent to participants registered for email follow up not responding to the email. For those not using a computer regularly, phone follow up by telephonists will be used so that the pharmacist/therapist is not conducting follow up.

Sustained smoking reduction will be measured as self-reported daily cigarette consumption at 12 month follow up, with a reduction being counted as self-reported consumption lower than at baseline. Sustained reduction will be counted as achieved if during the last four months (i.e. reports at month 9-12) of follow up, a person is smoking less at every follow up occasion than at baseline, measured by self-report. If a monthly report is missing, a person will be counted as having achieved sustained reduction if all other reports show this is the case and the last report is not missing. If two reports are missing, a person will be counted as not having achieved sustained reduction. Mean cigarettes per day at the end of follow up will be calculated from the last follow up only. If cigarettes per day is missing, then this will be replaced by baseline cigarettes per day, but in sensitivity analysis, we will use last observation carried forward.

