Participants who have maintained abstinence for 4 weeks will be asked to attend the pharmacy for carbon monoxide (CO) verification if they are in the self-help arm or if they are in the supported arm but are not due for or have ceased to attend visits. Those who have maintained abstinence for 6 months (defined in the same way with a grace period and no more than five cigarettes smoked) will be asked to return for CO verification in the same way. Participants attending the pharmacy for a non-therapeutic reason i.e. to attend for abstinence verification will be paid £20 to compensate them for their time and any travel costs incurred.

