### Procedures for handling the data

#### Data Management

The trial will run as part of the portfolio of trials in the Primary Care Clinical Research and Trials Unit (PCCRTU), an NIHR recognised trials unit in Primary Care Clinical Sciences at the University of Birmingham. The data management will be run in accord with the standard operating procedures (SOPs), which are fully compliant with the Data Protection Act and International Conference on Harmonisation (ICH) and Good Clinical Practice (GCP). The source documents for the trial will be the case report forms (CRFs) which will be stored in the pharmacies in a locked cabinet in a locked office. The trial database will be securely held and maintained by the PCCRTU. Data cleaning will take place by a series of logical checks on the electronic data. (For example, a person cannot be recorded as prolonged abstinent smoker at 6 months if they were not in such a state at 8 weeks). Discrepant records will be checked with the source documents and the database amended if necessary. On completion of the trial and data checking, the CRFs will be transferred to Modern Records, a secure archiving facility at the University of Birmingham, where they will be held for 15 years and then destroyed. The database will be anonymised and a secure compact disc containing the link between identification number and patient identifiable information will be stored in modern records.

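### Six-month abstinence is counted from quit day but follow-up stops at 12 months, so quits after about week 26 cannot succeed, which tilts this one outcome against the 34-week programme

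*Protocol article*

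**What the plan says.** All references are to the protocol article.

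- **Clock.** Trial Outcomes: "Smoking cessation outcomes will be measured from the time of quitting and we will measure 4 week and 6 month prolonged abstinence". The definition works by "allowing a two week grace period after quit day in which smoking lapses do not count against abstinence".
- **Observation.** Follow up procedures: the form is sent "monthly for the 12 months of a participant's involvement in the trial". CO verification is requested once six months of abstinence have been maintained.
- **Denominator.** Data analyses, Statistics: cessation is analysed by intention to treat with everyone randomised in the denominator.
- **Standard programme.** Supported standard programme: "providing support and monitoring at baseline, 2, 6, 10, 16, 22, 28, and 34 weeks". No support arms: "Participants will be advised to reduce on a schedule that follows the standard programme, if randomised to that arm".
- **Short programme.** Supported short programme: cessation is the aim at week 4, then at week 8. After that, participants may follow the standard regime.
- **Quit timing.** Transferring to the cessation programme: timing is left to therapist and patient, and a failed quit does not end the programme.

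Nothing in the article extends follow-up for late quitters, sets a latest qualifying quit date, or says how a quit after month 6 is classified.

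**The concern.** Programme length is one of the two randomised factors, and it governs when people are expected to quit. If the observation window closes at a fixed time after entry while the outcome clock starts at quit day, the chance of being seen to succeed depends on allocation as well as on the participant's behaviour. A standard-arm participant who quits at week 34 and stays abstinent is recorded as a six-month failure. A short-arm participant who quits on target always has time to qualify.

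This matters beyond the pilot. Comparing programme lengths on cessation is a primary objective. The Sample size section says a trial of these questions would need six-month prolonged abstinence as its outcome, and the Statistics section says updated estimates will set the size of a definitive trial. The Sample size section also already assumes that short programmes are about twice as effective, so an advantage produced by the window would look like confirmation.

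**Working it through.** The plan gives no figure for this point. Table 1 concerns four-week abstinence and is not used here.

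**Step 1: latest quit that can qualify.** Inputs: 52 weeks of follow-up (Follow up procedures), six months = 26 weeks, grace of 2 weeks (Trial Outcomes).

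- Latest quit = 52 − 26 = week 26.
- If the grace is added on top: 52 − 28 = week 24.

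**Step 2: follow-up left after each programme point.**

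| Quit at | Weeks left (52 − quit week) | 26 weeks available? |
|---|---|---|
| Week 4 (short, first target) | 48 | yes |
| Week 8 (short, second target) | 44 | yes |
| Week 28 (standard visit) | 24 | no |
| Week 34 (standard, last visit) | 18 | no |

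Observing six months after a week-34 quit needs 34 + 26 = 60 weeks.

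**Step 3: four-week outcome.** Latest qualifying quit = 52 − 4 = week 48, or 52 − 6 = week 46 with the grace added. A week-34 quitter has 18 weeks and can reach it.

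**Step 4: illustrative size.** The article gives no distribution of quit dates, so the late shares are assumptions. The true six-month rate is set at 7% in both arms. The Sample size section gives this figure for the supported standard programme; using it for both arms is my assumption. Let f be the share of standard-arm successes quitting after week 26, and g the same share in the short arm.

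- Observed standard rate = 7% × (1 − f).
- Spurious risk ratio, short versus standard = (1 − g) / (1 − f).

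| f | Observed standard rate | Risk ratio, g = 0 | Risk ratio, g = 10% |
|---|---|---|---|
| 10% | 6.3% | 1.11 | 1.00 |
| 20% | 5.6% | 1.25 | 1.13 |
| 30% | 4.9% | 1.43 | 1.29 |
| 50% | 3.5% | 2.00 | 1.80 |

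**Step 5: in people.** With about 80 per arm, 7% is 80 × 0.07 = 5.6 successes. Losing 10% to 50% of them is 0.6 to 2.8 participants, a risk difference of 0.7 to 3.5 percentage points. The 95% half-width for a difference between two arms of 80 at 7% is 1.96 × √(2 × 0.07 × 0.93 / 80) = 7.9 points.

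**The case against.** **This is a pilot, declared unpowered for abstinence, and four-week abstinence is its main efficacy outcome.** Correct. A reader might infer that the whole short-versus-standard comparison is compromised. The documents do not support that: Step 3 shows that the main efficacy outcome is essentially untouched, and Step 5 shows that the distortion lies within the pilot's sampling error. But lack of power does not excuse bias. More participants would not remove it, and a larger trial using the same window would inherit it.

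**Late quits may be few, or common in both arms.** This also stands. No quit date is set for the standard programme, and short-arm participants who have not quit by week 8 may move to the standard regime and quit late too. Both shrink the bias. It disappears only if late quits are equally common in both arms, which is not what the two schedules would lead one to expect.

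**Follow-up may be longer than 12 months.** Length of study places the final follow-up one year after recruitment ends. Read as a calendar cut-off, that would give early recruits more time. Follow up procedures nevertheless fixes 12 months per participant, and the last recruits have 12 months on either reading.

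**The full protocol or analysis plan may deal with it.** An analysis plan can classify late quitters, but it cannot supply observation time. The point rests on two stated values that do not fit together, not on something left out.

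**The data check.** Data Management gives as an example that "a person cannot be recorded as prolonged abstinent smoker at 6 months if they were not in such a state at 8 weeks". A reader might infer that everyone quitting after week 8 of the trial would be flagged. The documents do not support this: cessation is measured from quitting, the check is coherent on that clock, and discrepant records are checked against source and not failed automatically.

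**Conclusion.** The concern holds for six-month prolonged abstinence only. With 12 months of follow-up and a quit-day clock, a quit after about week 26 (week 24 with the grace added) cannot count as a success. The standard programme continues to week 34 while the short programme aims for week 4 or 8. The lost observation time therefore follows the randomised factor and lowers the standard arm's rate.

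The direction rests on late quits being more common in the standard arm, as the schedules imply. The size cannot be derived from the documents. A spurious risk ratio of about 1.1 to 2.0 follows from a true 7% in both arms, 10% to 50% late quits among standard-arm successes and none in the short arm. It falls towards 1.0 as late quits in the short arm increase. No single value in that range should be read as an estimate.

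This should be corrected because the six-month figure is meant to inform the definitive trial. It is not a threat to the pilot's feasibility aims or to its four-week comparison.

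**What to change.** 1. **Extend observation for late quitters.** For anyone in either arm in a continuing quit attempt at month 12, keep sending the same monthly form and offer CO verification until six months after quit day. State one cut-off for both arms: at least week 60 (34 + 26), or week 68 (8 + 34 + 26) if the short-arm fallback to the standard regime is to be covered. Repeat quits after the cut-off would still be missed, but under the same rule in both arms.
2. **Report quit timing.** Give by arm the distribution of quit dates and the number of quitters with less than six months of follow-up left. Do not carry the unadjusted six-month short-versus-standard estimate into the definitive trial's sample size without this.
3. **If an outcome at a common time from randomisation is added, state its minimum duration of abstinence.** Requiring six months of abstinence at month 12 would recreate the same truncation.

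**Cost.** About two extra automated forms per affected participant to week 60, or four to week 68, and a few verification visits at £20.

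**Calendar.** The waves use 6 + 4 + 12 = 22 months if spaced start to start, or 4 + 6 + 4 + 12 = 26 if the second starts six months after the first closes. Week 60 adds 8 weeks (about 2 months), giving 24 to 28. Week 68 adds 16 weeks (about 3.7 months), giving about 26 to 30. Both fit the stated 30 months, though week 68 with the wider spacing leaves almost no slack.
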